### Outcome measures

The primary outcome is self-reported smoking abstinence of 6 months duration, irrespective of treatment utilization (i.e., smoking abstinence among all smokers including those who use and those who do not use treatment), measured at 12 months, determined from the follow-up survey 12 months after randomization. Following the Society for Research on Nicotine and Tobacco (SRNT) Measures Workgroup Recommendations, the primary outcome is defined as having not smoked at least part of a cigarette on each of 7 consecutive days and having not smoked at least once on a weekend day over 2 consecutive weekends in the past 6 months [15]. Secondary measures of abstinence include self-reported 7-day point prevalence and 30-day point prevalence, defined as having not smoked a part of a cigarette in the past 7 days and as having not smoked a part of a cigarette in the past 30 days, respectively.

Other outcomes for this study comprise utilization and initiation of tobacco cessation treatment (from any source, including supplemental care from outside the VA) during the 12 month follow-up, specifically: 1) initiation of combined intensive behavioral counseling and medication treatment, 2) initiation of intensive behavioral counseling, and 3) initiation of medication treatment. Since some smokers may seek treatment from non-VA providers due to the proactive strategies tested, the secondary outcomes are primarily assessed using self-report from the 12-month follow-up survey. Initiation of medication treatment is defined as using one or more tobacco dependence medications (e.g., NRT and bupropion) in the 12-month follow-up period (from any source, VA and non-VA). Initiation of intensive counseling is defined as the completion of at least one call from a telephone counseling program or making at least one visit to a smoking cessation program in the 12-month follow-up period (from any source, VA and non-VA). In addition, we are assessing VA tobacco treatment utilization using VA administrative data--pharmacy dispensing records and visits to smoking cessation clinics

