The primary analysis will be by intention-to-treat. Since population-level smoking abstinence rates are expected to be small, z-tests comparing the strata-weighted differences between the two groups are less appropriate than comparisons based on odds ratios. The study design is a randomized complete block design, however, the patient populations within site vary and hence the proportion of the site population included in the study varies across site. Different intra-block (stratified) logistic analyses have been devised for similar survey designs for sampling from finite populations [32,33]. Herein these survey design-based logistic analyses are referred to as survey-logistic regressions. We will use survey-logistic regression methods to estimate and test intervention effects and racial/ethnic differences in the intervention effects on both smoking abstinence (e.g., 6-month prolonged abstinence, 7-day and 30-day point prevalence abstinence) and treatment utilization rates. These regression models will take into account the design stratification and the relative stratification populations. The models also will include any relevant covariates to adjust for confounding, if warranted. In this event we will use cross validation methods and standard model diagnostic methods to identify a well fitting model. Inference with respect to the impact of the intervention will be based on point estimates of the odds ratio for the effect of proactive outreach on the outcome relative to usual care, along with 95% confidence intervals and corresponding standard test results.

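### The primary outcome is named 6-month abstinence, but its written rule passes weekday-only smokers, alternate-weekend smokers and people who resumed smoking fewer than 7 days before the survey

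*Protocol article*

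**What the plan says.** All of the defining text is in the protocol article, under Outcome measures.

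- **Name:** "The primary outcome is self-reported smoking abstinence of 6 months duration", determined from the survey 12 months after randomization.
- **Stated basis:** "Following the Society for Research on Nicotine and Tobacco (SRNT) Measures Workgroup Recommendations".
- **Rule, first limb:** "having not smoked at least part of a cigarette on each of 7 consecutive days".
- **Rule, second limb and window:** "having not smoked at least once on a weekend day over 2 consecutive weekends in the past 6 months".
- **Point prevalence:** the 7-day measure, "having not smoked a part of a cigarette in the past 7 days", and a matching 30-day measure are secondary outcomes. Neither is part of the primary rule.

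The Analytic overview gives the primary outcome a slightly different name and lists it beside the other two: "6-month prolonged abstinence, 7-day and 30-day point prevalence abstinence". Each is to be analysed by survey-logistic regression. The Sample size and power analysis section assumes 3% abstinence under usual care, a 2-point absolute gain and 1500 participants per group.

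**The concern.** A prolonged-abstinence measure may reasonably forgive a lapse. This rule forgives more than that: smoking on every weekday of the window triggers neither limb. Because nothing is required at the time of the survey, a participant can be a primary success and a failure on the 7-day measure on the same form.

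Eligibility does not rule such people out. Under Study participants, the sample is current smokers identified from the medical record, with few exclusions and no requirement of daily smoking. An eligible weekday-only smoker who changes nothing would be scored as a 6-month success.

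With an assumed control rate of 3% and a target gain of 2 points, even a small share of wrongly passed participants would be large relative to the quantities being compared. It would raise the apparent abstinence rate in both arms and reduce power.

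The wording adds a separate risk. The first limb can be misread as requiring 7 consecutive smoke-free days, which is a different condition from having no run of 7 smoking days.

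**Working it through.** **1. The plan's own figure.** Inputs from Sample size and power analysis: p1 = 0.03, p2 = 0.05, type one error 0.05. Two-sided testing is assumed because sidedness is not stated. With p̄ = 0.04, pooled variance under the null and no continuity correction:

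n = [1.96·√(2·0.04·0.96) + 0.8416·√(0.03·0.97 + 0.05·0.95)]² / 0.02² = (0.5432 + 0.2329)² / 0.0004 ≈ 1506 per group.

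Power at 1500 per group is 79.8%. The stated 1500 reproduces, so the sample-size arithmetic is not in question.

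**2. The rule applied to smoking patterns over 26 weeks (182 days).**

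| Pattern | Longest smoking run | Smoking on 2 consecutive weekends? | Primary rule | Secondary measures |
|---|---|---|---|---|
| Every Monday to Friday, never at weekends | 5 days | No | Abstinent | Fails 7-day and 30-day |
| Every other weekend only | 2 days | No | Abstinent | Fails 30-day always, 7-day on some survey dates |
| Otherwise abstinent, daily smoking resumed 1 to 6 days before the survey | 1 to 6 days | No | Abstinent | Fails 7-day and 30-day |
| Daily smoking for 7 days or more | 7 days or more | Depends on length | Fails | Fails both if still smoking |

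The third row holds because a run touching two weekends must last at least from Sunday to the following Saturday, which is 7 days.

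The Monday-to-Friday smoker smokes on 26 × 5 = 130 days, and 130/182 = 71%. A search over all patterns that avoid both limbs gives a maximum of 143 or 144 smoking days of 182 (about 79%), depending on the weekday on which the window starts.

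**3. Illustration of size.** The shares of 1% and 2% are assumptions; the documents give none. Suppose that share of each arm passes wrongly on top of true rates of 3% and 5%, with the 2-point difference unchanged. Power = Φ{[0.02 − 1.96·√(2p̄(1−p̄)/1500)] / √([p1(1−p1) + p2(1−p2)]/1500)}:

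- 3% v 5%: (0.02 − 1.96 × 0.007155)/0.007146 = 0.836, power 79.8%
- 4% v 6%: (0.02 − 1.96 × 0.007958)/0.007950 = 0.554, power 71.0%
- 5% v 7%: (0.02 − 1.96 × 0.008672)/0.008664 = 0.347, power 63.6%

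**4. What a 7-day condition would remove.** It removes the first and third patterns, because both include smoking in the week before the survey. It removes the alternate-weekend smoker only in part. In a 14-day cycle with smoking on one Saturday and Sunday, the preceding 7 days contain a smoking day on 8 of the 14 possible survey dates.

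**The case against.** **The outcome is prolonged abstinence, and lapses are meant to be tolerated.** The Analytic overview uses that name, and the rule is attributed to a published recommendation. This stands as far as lapses go: continuous abstinence was not promised. It does not extend to weekday smoking throughout the window, which is not a lapse.

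**The cited source is not at hand, and the article may condense it.** This also stands. Whether the source words the weekend limb this way, or carries a condition on current smoking, cannot be checked here. The fix therefore begins with that check.

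**The 7-day and 30-day outcomes would expose a divergence.** They would help a reader notice one. They do not change who counts as a success on the primary outcome.

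**The size is hypothetical.** This stands. Nor is the 3% base rate tied to a stricter definition. It may already include people who pass this rule without quitting, in which case adding 1 or 2 points counts them twice.

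Three stronger readings are tempting, and the documents support none of them:

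- *Smokers at the time of the survey generally count as abstinent.* Anyone with a run of 7 smoking days, or weekend smoking on two consecutive weekends, fails. Only current smokers whose pattern avoids both limbs pass.
- *The rule favors the proactive arm.* That would need counseling to move smokers into patterns that avoid both limbs. Nothing in the protocol article indicates this.
- *The repair costs one survey word.* Under Study design overview, outcome data are described as already being collected, so rewording an item could mix two instruments.

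**Conclusion.** The point holds in limited form. As written, the primary rule scores three kinds of smoker as abstinent for 6 months: regular weekday-only smokers, alternate-weekend smokers, and otherwise abstinent people who resumed fewer than 7 days before the survey. Nothing elsewhere in the document adds a condition on current smoking. This follows from the text alone and needs no assumption about prevalence.

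The effect on the trial's result is unknown. The fall in power from 80% to 71% or 64% rests on assumed shares of 1% or 2% in each arm, a true control rate of 3% and an unchanged 2-point gain. It shows sensitivity and is not an estimate. No direction of bias between the arms can be claimed. The point should be addressed because the definition of the primary outcome is affected and a derivation from a measure already planned repairs most of it.

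**What to change.** 1. Restate the rule as a failure rule: a participant fails if, in the past 6 months, they smoked on each of 7 consecutive days, or smoked on at least one weekend day in each of 2 consecutive weekends. Check the weekend wording, and whether a current-smoking condition applies, against the cited recommendation. Use one name, prolonged abstinence, throughout, and say that lapses are allowed.
2. Count as abstinent only those who also report no smoking in the past 7 days on the 12-month survey. At minimum, prespecify that version as a key sensitivity analysis. First confirm that the shortened follow-up form, used by mail or telephone for late responders, carries the 7-day item; the Data collection section does not list its content.
3. Change the weekend limb to smoking on any day in each of 2 consecutive weeks only if the survey is not yet in the field.

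**Cost:** abstinence rates in both arms would be slightly lower, and the change to the published primary derivation must be documented and made before outcome data are analysed by arm. Step 2 alone leaves some misclassification, for example alternate-weekend smokers surveyed more than a week after they last smoked. The report should say so.

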### Potential moderators and confounders

#### Background factors

The following patient demographics are assessed in the survey: race, ethnicity, marital status, education, annual household income, and employment status. Alcohol consumption is assessed using the AUDIT-C [16]. VA administrative data sources are used to provide information on age, sex, and co-morbid conditions (e.g., ICD-9 codes).

#### Smoking behavior

Information regarding smoking history such as age of initiation, duration of smoking, previous quit attempts and prior use of tobacco treatment is collected using standard questions from the California Tobacco Survey [17] and the CDC Behavioral Risk Factor Surveillance Survey [18]. Nicotine dependence is assessed with the two-question Heaviness of Smoking Index: cigarettes per day and time to first cigarette after waking [19].

### Potential mediators

#### Provider factors

The provider factors examined include provider behavior related to delivery of smoking cessation care and communication style. Standard tobacco performance measures assess participants' receipt of smoking cessation advice, counseling and treatment from their VA primary care provider [20]. Questions from the Commonwealth Fund Survey are used to assess provider communication [21].

#### Cognitive factors

The cognitive factors examined in this study include motivation to quit, self-efficacy, attitudes toward NRT, mastery, and smoking stigma. Self-efficacy to quit and motivation to quit are assessed with a global measure of self-efficacy to quit [22], three self-efficacy subscales (situational self-efficacy which includes emotional and social self-efficacy and skill self-efficacy) [23] and the readiness to quit ladder [24,25]. Beliefs towards smoking cessation medications is assessed using the 12-item attitudes towards nicotine replacement therapy scale (ANRT-12) [26]. Mastery is measured using a standard 7-item questionnaire assessing the control one feels over one's life [27]. Smoking stigma, the concept that one feels stigmatized due to their smoking behavior, has been adapted from the Mental Health Consumers' Experience of Stigma [28].

#### Discrimination

In this study discrimination in the health care setting is assessed using the Physician Bias and Interpersonal Cultural Competence Measures Scale [21] which consists of 3 questions asking about being treated with respect by the doctor, the doctor's understanding of the participant's background and values, and feeling like the doctor looks down on the participant's way of life. Health care discrimination is also measured with a general question asking if the patient feels they have been discriminated against in a health care situation for any reason [29]. Day to day perceived discrimination is measured using nine questions that ask about the frequency of exposure to experiences of discrimination such as being treated with less courtesy, less respect, or being harassed [30].

#### Social environment

Participants' self-report their level of satisfaction with smoking cessation care from the VA on the follow-up survey [31]. Characteristics of the environment that make it difficult for them to participate in smoking cessation care from the VA are also being assessed (e.g., lack of transportation, and distance to site) [13]. Characteristics of the patient's social network assessed in the survey include: subjective norms related to smoking, smoking habits of friends and family, and home smoking rules.

### Analytic overview

With our proposed sample size (3200 per intervention group), random assignment can be expected to create two groups that are balanced with respect to observed and unobserved baseline characteristics. However, due to possible differential non-response among the two groups this balance may be missing between survey respondents within the two groups. To assess such imbalance, the respondents in the two groups will be compared with respect to key elements of the conceptual model and baseline measures a priori known to be related to smoking cessation and treatment utilization. Balance of the two groups will be tested using Mantel-Haenszel *χ*^2 ^tests for categorical variables which accounts for stratification by site and appropriate parametric tests (e.g. Blocked Anova F-tests) or nonparametric tests (e.g. Wilcoxon rank-sum test) for continuous variables. If the two groups are found to differ with respect to these relevant pre-intervention variables, then these variables will be included as covariates in the following analyses. These analyses and related comparisons of responders and non-responders will shed light on potential response bias issues. A usual practice in is to treat non-respondents at follow-up as continuing smokers. This practice is considered to be a conservative assumption; however, if usual care has significantly lower response rates to the follow-up survey than proactive care then this approach would favor the intervention. To address potential response bias issues, we will use standard statistical methodologies and implement propensity-based and imputation methods with imputation of smoking status or treatment utilization at follow-up. For VA treatment utilization outcomes, non-response is not an issue because we will obtain information from VA administrative databases on all randomized individuals.

The primary analysis will be by intention-to-treat. Since population-level smoking abstinence rates are expected to be small, z-tests comparing the strata-weighted differences between the two groups are less appropriate than comparisons based on odds ratios. The study design is a randomized complete block design, however, the patient populations within site vary and hence the proportion of the site population included in the study varies across site. Different intra-block (stratified) logistic analyses have been devised for similar survey designs for sampling from finite populations [32,33]. Herein these survey design-based logistic analyses are referred to as survey-logistic regressions. We will use survey-logistic regression methods to estimate and test intervention effects and racial/ethnic differences in the intervention effects on both smoking abstinence (e.g., 6-month prolonged abstinence, 7-day and 30-day point prevalence abstinence) and treatment utilization rates. These regression models will take into account the design stratification and the relative stratification populations. The models also will include any relevant covariates to adjust for confounding, if warranted. In this event we will use cross validation methods and standard model diagnostic methods to identify a well fitting model. Inference with respect to the impact of the intervention will be based on point estimates of the odds ratio for the effect of proactive outreach on the outcome relative to usual care, along with 95% confidence intervals and corresponding standard test results.

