## Methods/design

### Study design overview

This study is funded by the Department of Veterans Affairs (VA) Health Services Research and Development (HSR&D) and is registered in clinicaltrials.gov (NCT00608426). The Veterans Victory over Tobacco Study is a randomized controlled trial that compares the effects of a proactive care intervention including proactive outreach and choice of telephone care or face-to-face care for tobacco dependence treatment compared to reactive care (usual care). This study considers the population impact of smoking cessation treatment. Therefore, all smokers are included regardless of their interest in quitting. The study design (Figure 1) is a complete block design with subsampling in which 1600 individuals from each of four study sites are randomized to one of two groups (total N = 6400). Hence, each site constitutes a block and within each block 800 are assigned to the intervention group and 800 are assigned to usual care. Blocking by site controls for variation in outcomes due to differences between sites such as differences in smoking cessation programs and related factors. The VA's electronic medical record (EMR) Health Factors Dataset is used to identify current smokers at the four study sites [4] and all smokers identified are randomized prior to contact. Baseline data is obtained from VA administrative databases and from a participant survey that is conducted immediately after randomization. Outcome data is being collected 12 months after randomization from VA administrative databases and from a follow-up survey.

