### Sample size and power analysis

The power analysis assumes independent samples in the two groups from the four sites and considers a type one error rate of 0.05. A meaningful difference, from a public health perspective, is for PRO to produce a 2% increase in population-level smoking abstinence rates compared to UC. Using a base rate of 3% to estimate the sample size for this study, this study requires 1500 participants per intervention group (or total N = 3000) to have at least 80% power to detect a 2% or greater absolute difference in population-level smoking abstinence rates between groups. In addition, this study is well powered (> 90%) to detect clinically meaningful differences of 6% in treatment utilization rates using the most conservative base rate assumption of 50%. In order to achieve 3000 completed follow-up surveys from participants, we estimated that we need to include 6400 participants who will be sent the baseline survey. Among the 6400 participants who are mailed a baseline survey, we estimate approximately 5120 participants (20% exclusion rate due to subject refusal and misclassification of cigarette smoking status) will be sent a follow-up survey. We estimate a 60% response rate to the follow-up survey, which will result in about 3000 completed follow-up surveys.

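### Covariates enter the primary model only when a balance test among respondents is significant, and cross-validation then picks the model; a fixed prognostic covariate set should replace both steps

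*Protocol article*

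**What the plan says.** The Analytic overview expects randomization to balance the arms but allows that unequal non-response may unbalance those who answer the survey. Respondents are therefore compared by arm, with site-stratified Mantel-Haenszel tests for categorical variables and parametric or rank tests for continuous ones. The variables compared are elements of the study's conceptual model and baseline measures already known to relate to cessation or treatment use. The rule that follows is: "If the two groups are found to differ with respect to these relevant pre-intervention variables, then these variables will be included as covariates".

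The same section then describes survey-logistic regression that accounts for the site strata, with covariates added where judged warranted. On how that model is settled it says: "In this event we will use cross validation methods and standard model diagnostic methods to identify a well fitting model". Inference rests on the resulting odds ratio, its 95% confidence interval and the matching test. For response bias the section also commits to propensity and imputation methods.

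On timing, the Study design overview says baseline data come partly "from a participant survey that is conducted immediately after randomization". Under Potential mediators, the Cognitive factors section states: "The cognitive factors examined in this study include motivation to quit, self-efficacy, attitudes toward NRT, mastery, and smoking stigma".

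**The concern.** Two features of this rule are weak.

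First, entry depends on whether a difference between arms reaches significance. How much a variable confounds the comparison depends on the imbalance multiplied by the variable's effect on abstinence; the test sees only the imbalance, and that against its sampling error. A strong predictor with a real but modest imbalance can stay out, while a weak predictor with a chance imbalance comes in.

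Second, once any covariate enters, the outcome data help to choose the model. The covariate set behind the primary odds ratio is then unknown until the data are seen. This matters more for an odds ratio than for a risk difference, because adjusting for predictors changes the value that the odds ratio estimates even when the arms are balanced.

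At stake are a primary estimate that was not fixed in advance, and precision given up on predictors that are already being collected.

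**Working it through.** **Inputs from the Sample size and power analysis section.** The type I error: the section "considers a type one error rate of 0.05" (sidedness not stated). The control rate: "Using a base rate of 3% to estimate the sample size for this study". The target: "PRO to produce a 2% increase in population-level smoking abstinence rates compared to UC", that is 3% against 5%. The size: "this study requires 1500 participants per intervention group (or total N = 3000) to have at least 80% power".

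**The plan's own figure.** Two-sided, pooled variance, no continuity correction:

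n = [1.960 × √(2 × 0.04 × 0.96) + 0.842 × √(0.03 × 0.97 + 0.05 × 0.95)]² / 0.02² = 1506 per arm.

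Power at 1500 per arm is 79.8%. The stated 1500 reproduces, so 1500 respondents per arm is used below.

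**How often a real imbalance is flagged.** The level of the balance tests is not stated; 0.05 two-sided is assumed. With p̄ the mean of the two proportions:

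chance of flagging = Φ{ [d − 1.96 × √(2p̄(1 − p̄)/n)] / √[(p₁(1 − p₁) + p₂(1 − p₂))/n] }

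- 30% against 33%: (0.03 − 1.96 × 0.01696) / 0.01695 = −0.19, so 42%.
- 30% against 32%: (0.02 − 1.96 × 0.01689) / 0.01688 = −0.78, so 22%.

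The 30% prevalence is an assumption.

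**What a missed imbalance could do.** Assume abstinence of 8% in those with the factor and 1.5% in those without (neither figure is in the article). A 3-point imbalance shifts the contrast by 0.03 × (8.0 − 1.5) = about 0.2 points, and a 2-point imbalance by 0.02 × 6.5 = 0.13 points. Against the 2-point target these are about a tenth or less.

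**How often something is flagged when nothing is wrong.** With k independent tests at 0.05, the chance of at least one flag is 1 − 0.95^k: 23% for 5 tests, 40% for 10, 64% for 20 and 79% for 30.

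**What the rule costs.** A logistic simulation used 1500 runs, 1500 per arm, a 3% base rate and 10 independent covariates with log-odds 0.4 per SD. The conditional odds ratio was (0.05/0.95)/(0.03/0.97) = 1.70. All covariate inputs are assumed.

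| Adjustment | Type I error | Power | Mean log odds ratio |
|---|---|---|---|
| None | 5.2% | 72.8% | 0.487 |
| Test-selected | 5.1% | 72.7% | 0.488 |
| All pre-specified | 5.3% | 75.5% | 0.535 |

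Simulation error is about 0.6 points for type I error and 1.1 points for power. Power forgone is 75.5 − 72.7 = 2.8 points. The last column shows that the odds ratio being estimated depends on the covariate set. The simulation covers neither the cross-validated choice nor differential non-response.

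**Timing of the survey covariates.** In the Data collection section the reminder postcard follows the first mailing by about 10 days, and the second and third surveys follow at intervals of two to three weeks. The last mailing therefore falls at 10 + 14 + 14 = 38 to 10 + 21 + 21 = 52 days. In the Telephone outreach section, calls start 10 days after the packet, or sooner if the participant responds, and attempts run for two weeks, so to about day 24 after the packet. The article does not date the packet relative to the baseline survey.

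**The case against.** The strongest defence is that the rule has a purpose. It is aimed at systematic imbalance from unequal response, not at chance imbalance from randomization, and comparing respondents is a reasonable way to look for that. Known relation to cessation is part of how candidates are chosen, so prognosis is not ignored. Site is always accounted for, cross-validation applies only if covariates are used, and propensity and imputation methods are a second safeguard. All of this stands, and it means adjustment is not simply left to chance. It does not rescue the p-value as the entry criterion or the data-driven choice of the final model.

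The harm is also moderate: a missed imbalance of the size shown moves the contrast by about 0.2 points or less.

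A reader might infer two stronger charges. One is that the 5% error rate fails. The simulation shows no inflation from test-based selection, and the cross-validation step was not quantified either way. The other is that the plan adjusts away part of the intervention effect, because the survey follows randomization and measures potential mediators. The documents do not support that as a finding: the rule is confined to variables measured before the intervention, confounders are listed separately from mediators, the conceptual model is not spelled out, and the packet's date relative to the survey is not given. The study design figure is not available here, and an article condenses the full protocol. It remains an open question of timing.

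**Conclusion.** The point holds as a weakness in a stated rule, not as a missing detail. Covariate entry into the primary model turns on significance tests in the trial data, the model is then chosen by cross-validation and diagnostics, and only site is fixed. At 1500 per arm, real imbalances of 2 to 3 points at 30% prevalence go unflagged more often than not (78% and 58% of the time), given tests at the 0.05 level. The primary odds ratio is therefore data-dependent, and about 3 points of power are forgone under the assumed covariate strengths, in a design whose power at 1500 per arm is 79.8%. The change is worth making, but nothing here shows that the trial's conclusion would be invalid. Whether survey covariates could already reflect the outreach depends on a date that the article does not give.

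**What to change.** For the primary analysis, replace the balance-test trigger and the cross-validated choice with one pre-specified model: arm, site and a short list of prognostic covariates.

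- Take age, sex and comorbidity from administrative data dated before randomization.
- Add baseline survey items such as heaviness of smoking and prior treatment use only where they refer to, or were answered in, the period before the invitation packet. Impute missing values.
- Do not use survey measures listed as potential mediators as primary covariates unless they were answered before the packet.
- State when the packet is sent relative to the baseline survey and its reminders.
- Keep the balance comparisons, and the propensity and imputation work, as description and sensitivity analyses for response bias. Report the arm-plus-site model alongside.

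The cost is about a paragraph of wording, since these variables are already collected. The downside is that an imbalanced variable outside the list is adjusted for only in sensitivity analyses.
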